### **4.4 Sample size calculation**

Sample size calculations are based on the expected effects of the intervention on the main outcome measures, incidence of affective disorders and increasing time to incident problems. Incidence estimates are derived from the literature and other studies performed by our group (Prevention of anxiety and depression in late life). Effect estimates are based on the primary studies of Mittelman (1996, 2004). We estimate the yearly incidence of affective disorders among caregiver at risk conservatively at 30% (Cuijpers 2005). We aim to reduce the incidence to 10% of new cases a year. With an alpha of 0.05, power of 80%, 73 persons per group are then needed. Assuming 15% loss to follow up we need to recruit  $2 \times 73 \times 100 / 85 = 172$  pairs of dementia patients and family caregivers (Statpower software). This number will be sufficient as well to measure a moderately strong reduction (Cohen's  $D > 0.5$ ) in number of depressive or anxiety symptoms.

## **5 INTERVENTION**

### **5.1 Description**

The purpose of family counseling is to help family members provide emotional and instrumental support to the primary caregiver, the family member who carries the greatest weight of the caregiving, and to help all family members adapt to the changes that the demented process imposes on them.

The four family counseling sessions will follow the manual (Mittelman 2003). Four family meetings are scheduled within 8 months and run by a counselor with an advanced degree in nursing, social work or allied professions. Counselors receive a training based on the manual and train their skills prior to the study. One counselor is assigned to one caregiver to establish an ongoing relationship with someone who is familiar with the situation. The aims of the family meetings are: 1) to educate families about dementia consequences and resource information for care support; 2) to mobilize naturally existing family networks of patient and primary caregiver in order to improve emotional and instrumental support; 3) to teach problem solving and techniques for troublesome patient behavior that can be used after family counseling ends. The content of the sessions is also determined by the needs of each caregiver. For example, learning techniques, for management of troublesome behavior, promoting communication between family members. All sessions are audio-taped for supervision, intervision and detailed analysis.

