## 3 STUDY DESIGN

### 3.1 Design

Randomised controlled indicated prevention trial.

After selection and baseline assessment, study subjects are randomised to one of two groups; the intervention group receives usual care plus family meetings, the control group receives usual care only. Participants are free to seek additional assistance and support elsewhere at any time throughout 24 months follow-up. The study subjects are recruited through several memory clinics and specialized mental health care institutions.

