## **6.5 Statistical Analysis**

Intervention effects will be analysed with survival analysis (Cox Proportional Models) for the time to incident affective disorder and repeated measurement analyses for number of symptoms. Both techniques can adjust for possible baseline imbalance, and potential modifiers (e.g. gender caregiver, relation with patient, patient centre). Dropout and loss to follow up will be described.

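### Sample size and named models make no allowance for counsellors shared by intervention caregivers; if caseloads exceed one and outcomes correlate within counsellor, standard errors are understated

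*Protocol*

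**What the plan says.** - **Delivery (Protocol 5.1, 5.3).** Counsellors are memory-clinic staff trained from a manual. Continuity is deliberate: "One counselor is assigned to one caregiver to establish an ongoing relationship with someone who is familiar with the situation". Part of the session content is adapted to the individual caregiver. The number of counsellors and the caseload of each are not stated.
- **Allocation (3.1).** After baseline, "study subjects are randomised to one of two groups". The control group receives usual care only, so any counsellor effect lies in one arm.
- **Sample size (4.4).** The assumed annual incidence is 30% under usual care, with a target of 10% under the intervention. The resulting requirement is: "With an alpha of 0.05, power of 80%, 73 persons per group are then needed". After 15% loss this becomes 172 pairs. On symptoms: "This number will be sufficient as well to measure a moderately strong reduction", defined as Cohen's d above 0.5. No ICC or design effect appears.
- **Analysis (6.5).** "Intervention effects will be analysed with survival analysis (Cox Proportional Models) for the time to incident affective disorder", with repeated-measures analysis for symptoms. Caregiver gender, relation to the patient and centre are given as examples of adjustment factors. Counsellor is not among them, nor is it in the list of confounders and modifiers in 6.1.

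**The concern.** When one counsellor serves several families, part of that counsellor's skill and style is common to all of them. Their outcomes are then correlated in the intervention arm but not in the control arm, which is a partially nested design. An analysis that treats those caregivers as independent counts counsellor-to-counsellor variation as if it were information about the treatment. The intervals are then too narrow and the test rejects too often. A sample size computed under independence carries no margin set aside for this. The symptom scales are exposed as well as the disorder endpoint, because 6.1 lists both under the main study parameter.

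**Working it through.** **1. Reproduce the plan's figure.** Inputs from 4.4: 30% versus 10%, alpha 0.05 (two-sided assumed), power 80%.

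- Without continuity correction: n = [1.96·√(2·0.2·0.8) + 0.8416·√(0.21 + 0.09)]² / 0.2² = 61.6, so 62 per group.
- With continuity correction: (61.6/4)·[1 + √(1 + 4/(61.6·0.2))]² = 71.2, so 72 per group, against 73 stated.
- Loss to follow-up: 146/0.85 = 171.8, so 172 pairs.

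The stated figure is therefore an independent-subject comparison of one-year proportions, with nothing left over for a design effect.

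**2. Are counsellors shared?** The intervention arm has 172/2 = 86 caregivers. One counsellor per caregiver would need 86 trained counsellors at what 3.3 calls several institutions, and section 1.1 puts the whole country at about 40 memory clinics. Caseloads of 5, 10 or 20 would need about 17, 9 or 4 counsellors. Sharing is an inference, but a strong one.

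**3. Formulas.** Let m be caregivers per counsellor; m and the ICC are assumptions throughout.

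- Design effect in the intervention arm: DE = 1 + (m − 1)·ICC.
- True over naive variance of the difference, equal arms: R = (1 + DE)/2.
- Type I error with naive errors: 2·[1 − Φ(1.96/√R)].
- Power for d = 0.5 at one time point, clustering accounted for: Φ(0.5·√(73/2)/√R − 1.96).
- One-year proportions: the continuity-corrected test with 73 controls and an effective 73/DE in the intervention arm.
- 24-month Cox, rates held for two years: events 73·(1 − 0.7²) = 37.2 and 73·(1 − 0.9²) = 13.9; hazard ratio taken as 1/3; power Φ(ln 3/√(1/37.2 + DE/13.9) − 1.96). This is an approximation.

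**4. Results at 73 per group.**

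| m, ICC | DE | R | Type I error, symptom score | Power, d = 0.5 | Power, one-year 30% v 10% | Power, 24-month Cox |
|---|---|---|---|---|---|---|
| none | 1.00 | 1.00 | 5.0% | 85.6% | 81.1% | 93.7% |
| 5, 0.01 | 1.04 | 1.02 | 5.2% | 84.9% | 80.1% | 93.1% |
| 5, 0.05 | 1.20 | 1.10 | 6.2% | 82.1% | 76.0% | 90.4% |
| 10, 0.05 | 1.45 | 1.225 | 7.7% | 77.9% | 69.5% | 85.8% |
| 10, 0.10 | 1.90 | 1.45 | 10.4% | 70.8% | 58.5% | 77.5% |
| 20, 0.05 | 1.95 | 1.475 | 10.7% | 70.1% | 57.3% | 76.6% |

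At DE 1.7 the Cox power is 81.1%; it reaches 80% at about DE 1.76.

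**The case against.** **The sentence in 5.1 describes continuity, not sharing.** Read literally it is one counsellor per caregiver, so m = 1 and no clustering. This stands as far as the text goes: the protocol states no caseload. As a description of how 86 families would be served it is implausible, so the point has to be put conditionally rather than dropped.

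**Variance methods belong in the SAP.** Section 6.5 names model families and an open list of adjustments; both families accept a random effect, a frailty or a robust variance. This largely stands for the modelling detail. It does not cover 4.4, which fixes the power in the protocol itself, or the recording of the counsellor, which has to happen during the trial.

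**Centre adjustment and standardised delivery may absorb much of it.** Counsellors are clinic staff, so some of their variation lies between centres, and the manual, training and supervision all push the ICC down. This is fair, and it is a reason to take the low end of the range seriously. A centre term common to both arms still does not represent differences between counsellors within a centre, or variation present in one arm only.

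**A stronger reading.** A reader might infer that the intervals are certainly too narrow and that the trial does not have its stated 80% power. The documents do not support that. With small m and ICC the effect is negligible. Section 4.4 attaches no power figure to the symptom claim, and the calculation at d = 0.5 starts from about 85%, not 80%. The planned disorder test is a 24-month Cox model with more events than the one-year comparison that gave 73.

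**Conclusion.** The point holds in conditional form. Section 4.4 is an independent-subject calculation and nothing in 6.5 goes below centre. If counsellors see several caregivers and the ICC is positive, naive standard errors for the intervention effect are too small.

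The size cannot be fixed from the protocol. For a symptom score it runs from negligible (5 per counsellor, ICC 0.01) to material (10 per counsellor, ICC 0.05 to 0.10), where the test rejects at about 7.7% to 10.4% and power for d = 0.5 is about 78% to 71%.

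For the disorder endpoint, the calculation behind 73 per group drops from 81% to about 70% at 10 per counsellor and ICC 0.05. The planned 24-month Cox analysis has room to spare, so no shortfall below 80% is shown there up to a design effect of about 1.7. That rests on the 30% and 10% rates holding for two years and on a hazard ratio of 1/3. Spare power does not correct type I error or interval width, so the analysis change is still worth making. It is an inexpensive improvement, not a demonstrated failure of the design.

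**What to change.** - **Data (6.1).** Record the counsellor for each intervention caregiver.
- **Symptom scores (6.5).** Use a partially nested mixed model alongside the repeated measures: a random counsellor effect in the intervention arm only, each control as its own cluster, and small-sample degrees of freedom.
- **Time to disorder (6.5).** Use a counsellor-clustered robust variance with a small-sample correction, or a shared frailty in the intervention arm. Given the few events expected there (about 14), make this at least a sensitivity analysis.
- **Sample size (4.4).** State that 73 per group assumes no clustering by counsellor, give the expected caseload, and show power over a range of caseload and ICC.

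The cost is one identifier variable and a few sentences. Intervals will be slightly wider and the stated power slightly less favourable. No extra participants are needed.

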### **5.2 Intervention stages**

#### ***Preparation***

The first family session is prepared after the disclosure session with the patient and the caregiver. A follow up contact is planned soon after the disclosure session. The counsellor introduces the idea of seeking help from family members or friends and explains why this is beneficial. The caregiver defines and invites the family. A family can comprise good friends or neighbours as well. Counsellor and caregivers decide whether the patient attends the meetings as well. The counsellor recognizes the degree of openness in a family, the communication style, assesses the knowledge of dementia and is aware of individual coping styles.

#### ***Initial meeting***

Explanation of the purpose of the meetings, the protocol, scope of services that can be provided, ground rules and the counsellor's role; Introduction of all persons and expression of their perspectives on the situation; Clarification of issues and getting a consensus on which to address; Identification of objectives and helping family to allocate the tasks; Summary of observations and making plans for the next session.

#### ***Follow up***

Review of the previous session, previous commitments, task assignments, discussion of progress of carrying out tasks, identifying issues for current consideration. During the session it will become clear that some issues are resolved while others have taken a higher priority. In addition, new issues, problems, and conflicts will emerge. These are discussed in the same way as the original issues were in the first session. The counsellor concludes by discussing the date and time of the next session and who will attend. If the next meeting will be the last family session, the family should be reminded of that fact so that it does not come as a surprise and the can prepare for termination.

### ***Final session***

Acknowledge that this is the last session, give a summary of the observations about the progress that has been made and the goals that remain to be achieved; relate new issues to previously solved issues.

### ***Follow-up***

When needed additional ad hoc counseling for the family caregiver can be offered. Expectedly this will happen extremely incidentally.

## **5.3 Training**

An English Manual on how to do family meetings is available (Mittelman 2003). At the VUmc we have made a translation of the most important parts. Personnel of the memory clinics are trained according to this manual. Also [name] have already gained some experience with family meetings and will supervise ongoing meetings. Every site will pilot some meetings before the effect study will start. The VUmc site has already begun to pilot family meetings. So far we have met enthusiastic reactions from families.

## **5.4 Usual care**

The diagnostic assessments at memory clinics lead to a disclosure meeting with the patient and in most cases the primary family caregiver. Patients diagnosed with dementia and their accompanying family members are informed about the facilities that can help caring for the patients. Helpful leaflets, addresses, phone number and web sites are provided. Next, most patients are referred back to their General Practitioner. About a quarter of Alzheimer patients is prescribed anti-Alzheimer medication, and in such cases patient and family caregiver visit the memory clinic regularly for medication control visits. Family meetings are organised rarely and never in a structured way and with follow-ups. Moreover they tend to focus on providing clinical information and not on increasing family support.

## 6 METHODS

### 6.1 Study parameters/endpoints

#### Main study parameter/endpoint

- Incidence of major depression and anxiety disorders (i.e. generalised anxiety and panic) as defined according to DSM-IV criteria (APA 1994) and assessed with the Mini International Neuropsychiatric Interview (MINI) (Sheehan 1998). The MINI is used as 3 month prevalence measure.
- The *dimensional* or severity measure of anxiety and depression *symptoms* is derived by validated self report instruments: the Centre for Epidemiologic Studies Depression Scale (CES-D) (Radloff 1977) and Geriatric Depression Scale (GDS-5) (Hoyl 1999) for depression and the anxiety scale of the Hospital Anxiety and Depression scales (HADS) for anxiety (Zigmond 1983; Spinhoven 1997).

#### Secondary study parameters/endpoints

##### Caregiver

- Caregiver burden with the Short Sense of Competence Questionnaire (SSCQ) (Vernooij-Dassen 1999) and the Caregiver Reaction Assessment (CRA) (Given 1992)
- Quality of life with the Short Form 12 item version (Ware 1995)
- Quality adjusted life years with the SF-6D (SF-12)

##### Patients

- Depressive symptoms in patients (NPI)
- Quality of life with the Dementia Quality of Life Instrument (DQoL)

##### Other

- Days until institutionalization
- Resource utilization of patient and carer will be measured from a societal perspective with cost diaries (filled out by the carer) which include both direct (hospital visits) and indirect costs (travel time) and both within and outside (loss labour days) the health care.

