### Intervention

Four meetings with family and close friends will be organized and run by a trained counsellor according to a manual (Mittelman 2003). The aim is to offer psycho-education, increase problem-solving skills and mobilize the naturally existing social network of patient by sharing support tasks of network members.

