## **1 INTRODUCTION AND RATIONALE**

### **1.1 Motivation**

Our hypothesis is that affective disorders (i.e. depressive or anxiety disorders) of dementia caregivers who are already at risk for such disorders are largely preventable. Systematic reviews and meta-analyses show that information and support alone is helpful but only address the psychological needs of caregivers modestly at best (Sorensen 2002, Brodaty 2003). Programs that demonstrate beneficial effects on affective disorders involved both patients and their families, are more intensive and modified to caregivers needs (Brodaty 2003, Acton 2002). As demonstrated in the landmark studies of Mittelman et al., family meetings, designed to mobilize support of naturally existing family networks, appear to be among the most powerful psychosocial interventions to reduce depression in caregivers (Whitlatch 1991, Mittelman 1995, 1996, 2004). However, these studies have not been replicated elsewhere. Family counselling can maximise the positive contributions of each member to caregiving, prevent one member from carrying the entire weight of the caregiving role, improve the caregiver's understanding of how to ask for help, what kind of help is reasonable to expect from family members, and how to accept help, and reduce family conflict. In addition, these programs resulted in postponement of nursing home placement of patients, while maintaining a comparable or better quality of life of the caregivers.

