### 2.2 Secondary Objective

An economic evaluation will be performed alongside the study to estimate the cost-effectiveness.

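### The economic evaluation claims a societal perspective but states its cost scope as patient and carer, leaving out the relatives and friends through whom the intervention works

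*Protocol*

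**What the plan says.** Section 2.2 makes cost-effectiveness the secondary objective: "An economic evaluation will be performed alongside the study to estimate the cost-effectiveness".

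Section 6.1 (Other) sets the scope of cost measurement: "Resource utilization of patient and carer will be measured from a societal perspective with cost diaries (filled out by the carer". It goes on to describe the diaries as ones "which include both direct (hospital visits) and indirect costs (travel time) and both within and outside (loss labour days) the health care". That is all the protocol says about whose costs are collected.

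The intervention's mechanism appears in several places:

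- The Summary (Intervention) says the aim is to "mobilize the naturally existing social network of patient by sharing support tasks of network members".
- Section 1.1 says family counselling can "prevent one member from carrying the entire weight of the caregiving role".
- Section 5.1 lists among the aims "to mobilize naturally existing family networks of patient and primary caregiver in order to improve emotional and instrumental support".
- Section 5.2 (Initial meeting) includes "Identification of objectives and helping family to allocate the tasks". The later sessions review those assignments.

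On the meetings themselves, Section 5.1 says: "Four family meetings are scheduled within 8 months". Section 5.2 (Preparation) lets the caregiver invite friends and neighbours as well as relatives. Under Section 3.1, the control arm receives usual care without these meetings.

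**The concern.** A societal perspective counts costs whoever bears them. Section 6.1 claims that perspective and then names two people. In many trials the gap would be minor, because other people's costs would be similar in both arms. Here the people outside the stated scope are the ones the intervention is meant to activate, so their input should differ between arms by design.

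What is at stake is the incremental cost, and with it the cost-effectiveness ratio. If sharing tasks frees the carer to work or travel less for care, the diary can record that gain while the sibling's or neighbour's replacement effort goes unrecorded. Section 1.3 presents a favourable economic result as grounds for adding the intervention to Dutch care services, so a cost moved within the family should not be read as a cost saved. The primary endpoint and the sample size are not affected.

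**Working it through.** The protocol contains no cost figure, unit price or hours to reproduce, so the check is of scope, followed by direction and an illustration.

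**1. Who is covered.** Section 6.1 (Other) covers patient and carer. The study unit is the patient with the primary family caregiver, and the protocol refers separately to other family members, friends and neighbours. None of the named cost items is assigned to those others.

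**2. Whether another instrument fills the gap.** Section 6.1 (Potential confounders/modifiers) lists duration and hours of caregiving and a social support assessment of the caregiver. Both are covariates, not cost items, and neither is said to measure other people's hours.

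**3. Direction.** Let H be other helpers' time, travel and lost work per family, and v its unit value. If H is not collected, then

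measured cost difference = true cost difference − v × (H in intervention − H in control).

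Help that relatives would give in either arm cancels, so only the increment matters. It has two parts.

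- *Meeting attendance.* This is zero in the control arm and positive in the intervention arm. Its omission lowers the measured cost of the intervention.
- *Shifted care.* The effect depends on what the diary values:
  - If the carer's care hours are valued and others' hours are not, a moved hour shows as a saving.
  - If nobody's care hours are valued, a moved hour appears on neither side. A one-sided saving then arises only where the carer's lost labour days or travel fall.
  - If all helpers' hours are valued, shifted care causes no bias.

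The protocol does not say which case applies. Where there is a bias, tasks moving away from the carer push it towards family meetings.

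**4. Illustration of unrecorded hours.** All inputs except the four meetings and the 24-month follow-up are assumptions.

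- *Attendance:* relatives × meetings × hours each, including travel. Low: 2 × 4 × 1.5 = 12 h. High: 6 × 4 × 3 = 72 h per intervention family.
- *Shifted care over 24 months (104 weeks):* 1 × 104 = 104 h to 5 × 104 = 520 h per family. This supposes the shift is complete from the first week. If it began only after the 8 months of meetings, 104 × 16/24 = 69.3 weeks remain, giving about 69 to 347 h.

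These are hours outside the stated scope, not an estimate of the bias. By step 3, shifted hours become a bias only where the matching reduction for the carer is counted.

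**The case against.** The best counter-argument is that Section 6.1 names whose resource use is measured, not who supplies the resource. Care given by a sibling is something the patient uses, and the carer who completes the diary could report it. The bracketed items read as examples, and the diary form is not shown, so it may have a field for other helpers. Diary items and valuation rules are also often left to later documents.

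Part of this stands. One cannot say that the diary omits other helpers, only that the protocol does not include them. But relatives' time and travel to meetings are hard to read as the patient's resource use, especially as Section 5.2 leaves open whether the patient attends. The choice of valuation rule can wait for an analysis plan, but data capture cannot: hours that were never collected cannot be valued later.

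A reader might also infer that every hour moved from the carer to someone else will appear as a saving. The protocol does not support this, because it never says the carer's care hours are a valued cost item. Lost labour days and travel time are the named routes by which a shift would show. Nor is the whole of other helpers' input specific to one arm, since relatives help control families too.

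Finally, the protocol calls institutional care very costly and measures days until institutionalisation. A difference there could outweigh any omitted family time, so the omission need not reverse the economic result.

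**Conclusion.** The stated perspective and the stated scope do not match, and the mismatch falls on the people through whom the intervention works. Followed as written, the plan omits other attendees' meeting time and travel in the intervention arm and has no stated means of capturing care shifted to them. The likely direction favours family meetings.

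The size is unknown. The ranges of 12 to 72 h for attendance and 104 to 520 h for shifted care rest on assumed attendance, session length and weekly shift, and the second is not itself a bias. It would be tempting to conclude that the trial cannot support any societal cost-effectiveness statement, or that the cost is demonstrably understated. Neither follows while the diary form is unseen and no unit values are given. What follows is that a societal claim is not secured by the data collection described. This should be corrected, but it concerns the secondary economic objective only.

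**What to change.** In Section 6.1 (Other):

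- State that the carer's diary records, in both arms, the unpaid care hours, travel and lost work of other family members and friends.
- Have the counsellor log the number of attendees, the duration and the travel at each family meeting.
- State that informal care time is valued by one common rule, whoever provides it.

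If the diary already has such fields, amending the scope sentence to say so is enough for the first item. If the data will not be collected, restate the perspective as that of patient and primary carer and limit the cost-effectiveness conclusion to it.

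The cost is an extra diary line or two and a short attendance log. The carer's diary burden rises slightly, hours reported on behalf of others will be approximate, and the cost result may be less favourable. Sample size, randomisation and the intervention are unchanged.
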